### Study aim

This paper describes the research protocol for an RCT (the 40-Something Study) aimed at testing the feasibility and effectiveness of applying a health professional led, weight gain prevention intervention in non-obese women about to enter the menopause transition (aged 44–50 years). The feasibility of recruiting to the study, ability to retain participants and the suitability of the written materials were tested along with the preliminary effectiveness of the intervention. There are two hypotheses:

1. Women in the MI group will lose at least 2.5 kg by the end of the intervention (12 months post-baseline) and maintain that loss for a further 12 months (to 24 months post-baseline).

2. Women in the SDI (control) will gain 0.5 kg by 12 months and 1.0 kg by 24 months.

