### Sample size

The sample size calculation was based on the main outcome measure of body weight. Observational studies of women in this age group in the Australian population have demonstrated a mean (SD) weight gain of 1.04 (4.7) kg over a two-year period [22]. Given both intervention groups were comprised of equal numbers of healthy weight and overweight women and presuming the overweight women would meet the intervention goal of losing 5 kg^a^ in the first 12 months and the healthy weight women would show zero weight change, the net weight change should be a 2.5 kg weight loss in the MI group by the end of phase 1. Based on the Australian data of net weight gain in the general population of mid-age women managing their weight by self-directed means [21], we would expect a mean (SD) net weight gain of 0.5 (4.7) kg per year in our SDI (control) group. This would give an expected difference between the two groups of 3.0 kg after 12 months (end phase 1) and 3.5 kg after 24 months (end phase 2). Assuming equal sample sizes, to detect a difference in weight between groups of 3.5 kg with 80% power and a significance level of 0.05, a sample size of 22 women was required for each group. Allowing for an attrition rate of 20% by the end of 24 months, a total sample size of 55 women is required.

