### Outcome measures

Outcome measures were assessed for all participants at baseline, between May-September 2010, and reassessed at 3, 12, 18 and 24 months (end of monitoring phase 2) as shown in Additional file 3. The primary endpoints are at 12 months to determine the effects of the intervention and at 24 months to assess whether the intervention effects were maintained. Weight was the primary outcome measure.

#### **
*Measurement procedure*
**

Assessments were conducted in the early morning, in the anthropometry laboratory at the University of Newcastle (Australia). Procedures and protocols for the measurements were standardised, documented, and research assistants were trained in their application prior to collection. Participants fasted overnight, and upon entry to the laboratory removed their shoes and excess clothing. The assessment process lasted approximately 60 minutes for each participant, and they were provided with breakfast prior to leaving the laboratory.

#### **
*Anthropometry*
**

Height was measured using a stadiometer (Surgical and Medical Products) correct to 0.1 cm using the stretch stature method. Weight and body composition (percentage fat, skeletal muscle mass) were measured at all time points using BIA Omron HBR-500 Body Composition Monitor with Scales correct to 0.1 kg. BMI was calculated using the standard equation (weight [kg]/height[m]^2^). Waist circumference was collected as a valid marker of central adiposity [44] using a non-extensible steel tape to measure at the level of the mid-point between the lower costal border and the iliac crest (KDS F10-02, KDS Corporation, Osaka, Japan). Two measures were collected and averaged. Visceral adipose tissue area was estimated using the InBody720 Body Composition Analyzer (Biospace) at 12, 18 and 24 months.

#### **
*Biomarkers of metabolic syndrome*
**

Thirty millilitres of blood was collected from each participant by a trained phlebotomist and analysed by a laboratory accredited with the National Association of Testing Authorities Australia. Fasting measures of total cholesterol, low density lipoprotein cholesterol, high density lipoprotein cholesterol, triglycerides and glucose were assessed. Blood samples have been stored in a -80°C freezer for further analyses (sex hormones, insulin, leptin, and antioxidants to validate dietary intake) should funds become available.

#### **
*Blood pressure and resting heart rate*
**

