### Data analysis

Outcome measures collected at baseline will be compared to those at 12 months (after adjusting for baseline weight) to assess intervention effects and compared with measures at 24 months (end phase 2) to assess whether the intervention effects were maintained. Analyses will be conducted using the intention to treat principle, and performed using SPSS version 19 (IBM). All variables will be checked for plausibility. Continuous variables will be assessed for normality. Independent sample t-tests and chi-squared tests will be conducted on continuous and categorical variables (respectively) to check they do not vary by intervention group at baseline, and by completers versus attriters. Analysis of covariance will be used to examine whether the intervention groups differed significantly in weight at each of 12 and 24 months after adjusting for baseline weight. Behaviour changes in diet and physical activity will be assessed as secondary outcome measures using analysis of covariance to determine whether the MI and SDI groups differed significantly in dietary or physical activity behaviours at 12 months. Results will be stratified for baseline BMI category.

Logistic regression analysis will be performed to assess whether categorical variables, such as smoking status significantly influenced weight. The visceral adipose tissue variable will be assessed for between group differences at 12 and 24 months using independent sample t-tests, and analyses stratified by BMI category to determine whether the results differed for the healthy weight and overweight women. Sensitivity analyses will be conducted to determine the effects on the outcomes of different methods of treating loss to follow-up (last observation carried forward versus imputation). The relationship between weight outcomes and compliance with the diet and physical activity behaviours will be assessed using mediation analysis [55].

A per protocol analysis will be conducted on women who adhered to the requirements of their assigned group. Adherent women are defined as those who completed all required eating and physical activity diaries over the 12-month period and attended all assessment sessions, regardless of assigned group, and who attended all five health professional consultations for the MI group. Results of the protocol adherent group will be compared with non-adherers in each group, that is, those who did not meet the adherence recommendations.

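### The loss-to-follow-up check uses last observation carried forward, which presumes Phase 2 maintenance in women last seen at 12 months, while the 3- and 18-month weights have no stated role in the weight analysis

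*Protocol article*

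**What the plan says.** - **Visits.** Under Outcome measures, the outcomes (weight is the primary one) are taken at baseline and "reassessed at 3, 12, 18 and 24 months (end of monitoring phase 2").
- **Purpose of the late endpoint.** The same section places one primary endpoint "at 24 months to assess whether the intervention effects were maintained". The first hypothesis under Study aim is that MI women lose at least 2.5 kg by 12 months and "maintain that loss for a further 12 months". The second is that the self-directed (SDI) arm is up 0.5 kg at 12 months and 1.0 kg at 24 months.
- **Weight analysis.** Data analysis tests by ANCOVA "whether the intervention groups differed significantly in weight at each of 12 and 24 months after adjusting for baseline weight". That section gives the 3- and 18-month weights no role in this test.
- **Missing weights.** Data analysis also says "Analyses will be conducted using the intention to treat principle". Loss to follow-up is addressed only among the sensitivity analyses, which compare "different methods of treating loss to follow-up (last observation carried forward versus imputation"). The kind of imputation is not specified.
- **Expected loss.** The Sample size section plans for it: "Allowing for an attrition rate of 20% by the end of 24 months", a total of 55 women is required.

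**The concern.** A sensitivity analysis should put the main conclusion under strain. At 24 months that conclusion is about maintenance, and the method that would overturn a claim of maintenance is one that lets lost women regain weight. LOCF does the reverse for any woman last weighed at 12 months: it enters no change over Phase 2. In MI that is the hypothesis under test. In SDI it removes the 0.5 kg rise that the plan expects. The filled-in weights are then analysed as if measured, so their uncertainty is lost.

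The second strand is about information. A woman who attends at 3, 12 and 18 months but not at 24 has weights that bear on her 24-month value. An ANCOVA at a single follow-up visit does not use them unless a separate imputation step brings them in.

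At stake is whether agreement between the main result and its robustness check can be read as evidence that the effect lasted.

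**Working it through.** **Inputs from the protocol article**
- MI: −2.5 kg at 12 months, held to 24 months (Study aim).
- SDI: +0.5 kg at 12 months, +1.0 kg at 24 months (Study aim).
- Attrition 20% by 24 months; SD 4.7 kg; 22 per group (Sample size).
- 28 MI and 26 SDI women randomised (Abstract).

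**The plan's own figures.** 0.5 + 2.5 = 3.0 kg at 12 months and 1.0 + 2.5 = 3.5 kg at 24 months, as stated. (22 + 22)/0.8 = 55, as stated. How the 22 per group was reached is a separate matter and does not enter here.

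**LOCF error when the 12-month weight is carried.** Assume that all losses fall between the 12-month visit and the next one. Let r be the MI regain in Phase 2, with 20% lost in each arm.
- True 24-month difference: 1.0 − (−2.5 + r) = 3.5 − r.
- LOCF difference: 0.8 × (3.5 − r) + 0.2 × 3.0 = 3.4 − 0.8r.
- Error: (3.4 − 0.8r) − (3.5 − r) = −0.1 + 0.2r.

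| MI regain r (kg) | True | LOCF | Error |
|---|---|---|---|
| 0 (full maintenance) | 3.50 | 3.40 | −0.10 |
| 0.5 | 3.00 | 3.00 | 0 |
| 1.25 (half) | 2.25 | 2.40 | +0.15 |
| 2.5 (full) | 1.00 | 1.40 | +0.40 |

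The error depends only on the lost women. If only they regain the full 2.5 kg, the true difference is 3.5 − 0.2 × 2.5 = 3.0, LOCF gives 3.4, and the error is again +0.40.

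**Unequal loss.** With fractions lost d(MI) and d(SDI), the error is d(MI) × r − d(SDI) × 0.5. At full regain, 30% MI and 10% SDI loss gives 0.75 − 0.05 = +0.70 kg; 10% and 30% gives 0.25 − 0.15 = +0.10 kg.

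**Other carried values**
- Baseline carried (loss before 3 months), full maintenance: 0.8 × 1.0 − 0.8 × (−2.5) = 2.80 against 3.50. The contrast shrinks.
- 18-month weight carried, assuming linear Phase 2 change: 0.8 × (3.5 − r) + 0.2 × (3.25 − r/2) = 3.45 − 0.9r, an error of −0.05 + 0.1r, half of that above.

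**Precision of a repeated-measures model at 24 months.** Assumptions not in the document: 27 women per arm, 5 lost per arm (22 left), residual SD 4.7 kg, and a correlation of 0.70 to 0.95 between weights six months apart, decaying with time. Three timings of loss were tried.
- Observed-case ANCOVA: standard error 4.7 × √(2/22) = 1.42 kg.
- Repeated-measures model: variance 0.84 to 0.99 times as large, standard error 1.30 to 1.41 kg, effective number 22.2 to 26.1 per arm instead of 22. The gain is largest when the losses come after 12 months.

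**Return to baseline for lost MI women only, full maintenance.** MI mean 0.8 × (−2.5) = −2.0; difference 1.0 + 2.0 = 3.0 against 3.5, an error of −0.5 kg.

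**The case against.** The case on the other side is substantial, and most of it stands.

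- **LOCF is not the main analysis.** A reader might infer that the 24-month result rests on it. The text does not support that: LOCF appears only among the sensitivity analyses, as one side of a comparison with imputation.
- **The ANCOVA is not wrong.** A baseline-adjusted comparison at each of the two declared endpoints is valid. A reader might also infer that about 54 × 0.2 ≈ 11 women are dropped at 24 months. That presumes an observed-case analysis, which the article does not state. Handling of missing weights in the main analysis is commonly left to the full plan, and imputation could draw on the 3- and 18-month weights.
- **The error does not always favour MI.** On the plan's figures LOCF works against MI for any regain below 0.5 kg, including the hypothesised full maintenance. A carried 18-month weight already holds six months of Phase 2 change, and a carried baseline shrinks the contrast.
- **The size is modest.** +0.40 kg needs full regain in the lost women and every loss just after 12 months. It is about 0.28 of the assumed 1.42 kg standard error (0.40/1.42).
- **The alternative also has a direction.** Return to baseline in MI only errs by −0.5 kg if weight is in fact maintained. It is defensible only as a deliberately conservative case.

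This does not rescue LOCF as a robustness check. Its error changes sign with the amount of regain and the timing of loss, and it turns towards MI as regain grows, which is the failure that Phase 2 is there to detect.

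**Conclusion.** The point holds as a cheap improvement, not as an error in the main analysis. Separate ANCOVAs at 12 and 24 months are valid but leave weights already collected without a stated role. The sensitivity comparison includes a method that presumes maintenance in women last seen at 12 months and understates the uncertainty of their values.

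On the plan's means, with 20% lost per arm just after 12 months, the LOCF error runs from −0.10 kg under full maintenance to +0.40 kg under full regain, crossing zero at 0.5 kg. These figures rest on the hypothesised SDI course and on that timing of loss. The precision gain from using all visits is about 1–16% of the 24-month variance and rests on correlations that the document does not give.

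**What to change.** 1. Estimate the 12- and 24-month contrasts from one mixed model for repeated measures on the weights at 3, 12, 18 and 24 months, with arm by visit, baseline weight by visit, and BMI category. This answers the same two questions and keeps the partial records of women lost after the 3-month visit. State the covariance structure in advance, with a fallback should the model not converge.
2. Remove LOCF from the sensitivity analysis. Specify multiple imputation that uses all observed weights and BMI category, repeated over a range of assumed regain in the women lost. Include return to baseline, labelled as deliberately conservative, and report how much regain would change the 24-month conclusion.

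Cost: changes to the analysis wording and slightly more analysis work. With about 27 women per arm the model carries more parameters than a single ANCOVA (an unstructured covariance over four visits has 4 × 5/2 = 10), so a small-sample correction to the degrees of freedom should be named. No new data are required.

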## Discussion

The study described in this paper, the 40-Something study, is the first RCT aimed at preventing menopausal weight gain in Australian women and one of only a few internationally to do so. Importantly, this paper describes how an RCT of a relatively low intensity intervention, based on an existing health system model of health professional consultations, may lead to more successful weight control in pre-menopausal women than a self-directed intervention based on health education messages. The results of this trial will significantly add to the body of literature on methods of obesity prevention at menopause, which is an under-researched area.

The 40-Something study is also an innovative application of MI to prevent obesity, rather than treat it. By using a Dietitian and an Exercise Physiologist in applying the counselling framework to increase RCT effectiveness, the 40-Something study has implications for skills development of health professionals in practice settings. This RCT addresses some of the short-falls of the only other reported menopausal weight control intervention in that it tests a lower intensity intervention. Importantly, it will also ascertain whether the current healthcare system can support the delivery of effective menopausal weight prevention programs to address this significant public health issue.

Limitations of this review include the use of self-reported data for the weighed food record and the physical activity diaries relating to the issue of misreporting and social desirability response. It was not possible to achieve participant blinding for this study, increasing the risk of bias, though efforts were made to achieve researcher blinding. As with any measures, the tools we used are subject to bias and the TFEQ in particular requires further validation in a mid-age population. The compliance measurement at three months will likely be subject to social desirability bias given the diary recording, although the pedometers were included in an attempt to objectify the measurement of physical activity. The stored blood samples will allow for future antioxidant analysis as a validation of the four-day weighed food record data. The sample size meant the study was underpowered to assess differences in the secondary outcome variables, but it was sufficiently powered to detect weight differences according to the goals for each weight category. Study findings from phase 1 will be collated in 2012 and from phase 2 in 2013 and, if shown to be feasible, will help to inform the design of a larger randomized controlled trial to determine intervention effectiveness in preventing metabolic syndrome, and cost effectiveness of the intervention.

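### The Discussion's statement that the trial was sufficiently powered for the goals of each weight category is not supported by the article's own figures

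*Protocol article*

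**What the plan says.** The Discussion concedes low power for the secondary outcomes and then says that for weight "it was sufficiently powered to detect weight differences according to the goals for each weight category".

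The Sample size section builds one pooled effect from category-specific expectations in the MI arm, "presuming the overweight women would meet the intervention goal of losing 5 kg" by 12 months while "the healthy weight women would show zero weight change". With equal numbers in the two categories this averages to a 2.5 kg loss. For the control arm it says "we would expect a mean (SD) net weight gain of 0.5 (4.7) kg per year in our SDI (control) group", and the second hypothesis under Study aim repeats this: "Women in the SDI (control) will gain 0.5 kg by 12 months and 1.0 kg by 24 months". The resulting pooled differences are 3.0 kg at 12 months and 3.5 kg at 24 months. The calculation is "to detect a difference in weight between groups of 3.5 kg with 80% power and a significance level of 0.05", giving 22 women per group and 55 in total after 20% attrition.

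Under Data analysis the article adds: "Results will be stratified for baseline BMI category". No power or sample size is stated for either BMI category.

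**The concern.** The sentence attaches adequate power to the goals of each category, but the effects behind those goals are very unequal. In the MI arm the plan expects no change in healthy-weight women and a 5 kg loss in overweight women. Against a control gain of 0.5 to 1.0 kg, the healthy-weight contrast is small compared with an SD of 4.7 kg, and only about half of each arm contributes to it.

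Two things are at stake. Stratified results are planned, so a reader who trusts the sentence could take a non-significant healthy-weight result as evidence that the intervention does nothing there. The article also says the findings will inform a larger trial, so a mistaken belief about what this sample could detect might carry over into that design.

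**Working it through.** **Inputs from the article**

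- MI change: 0 kg (healthy weight), -5 kg (overweight) at 12 months. Hypothesis 1 has the loss maintained to 24 months (Sample size; Study aim).
- SDI change: +0.5 kg at 12 months, +1.0 kg at 24 months, given for the whole arm.
- SD of weight change: 4.7 kg, given for the whole arm.
- 22 evaluable per arm, categories equal in size: 22 / 2 = 11 per arm per category.
- Randomised: 28 MI, 26 SDI (Abstract), so about 14 and 13 per category with no dropout.
- Significance level 0.05; one- or two-sided not stated.

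**Assumptions added here:** the SDI gain and the SD of 4.7 kg apply within each category, and tests are two-sided unless noted.

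**Step 1. The article's own figure.** n per group = 2 × SD² × (z_alpha + z_power)² / difference².

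- One-sided: 2 × 4.7² × (1.645 + 0.842)² / 3.5² = 22.3, close to the stated 22.
- Two-sided: 2 × 4.7² × (1.960 + 0.842)² / 3.5² = 28.3, so 29.
- Attrition: 44 / 0.8 = 55, as stated.

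The stated 22 is thus reached, approximately, only with a one-sided test.

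**Step 2. Differences implied in each category (SDI minus MI)**

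- Healthy weight: 0.5 - 0 = 0.5 kg; 1.0 - 0 = 1.0 kg.
- Overweight: 0.5 + 5 = 5.5 kg; 1.0 + 5 = 6.0 kg.
- Check: (0.5 + 5.5) / 2 = 3.0 and (1.0 + 6.0) / 2 = 3.5, the article's pooled figures.

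**Step 3. Power within category.** Two-sample t-test, non-central t. With 11 per arm, SE = 4.7 × √(2/11) = 2.00 kg, df = 20, critical t = 2.086, non-centrality = difference / SE.

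| Category | Difference | Non-centrality | Power, 11 per arm | Power, 14 vs 13 |
|---|---|---|---|---|
| Healthy, 12 mo | 0.5 kg | 0.25 | 5.6% | 5.8% |
| Healthy, 24 mo | 1.0 kg | 0.50 | 7.6% | 8.3% |
| Overweight, 12 mo | 5.5 kg | 2.74 | 74% | 83% |
| Overweight, 24 mo | 6.0 kg | 2.99 | 81% | 89% |

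One-sided, the healthy-weight figures with 11 per arm are 8% and 12%. The smallest difference detectable with 80% power at 11 per arm is about 5.9 kg. For 1.0 kg, about 2 × 4.7² × 2.802² = 347 women per arm would be needed.

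**Step 4. Sensitivity to the SD.** Healthy-weight power with 11 per arm, for 0.5 and 1.0 kg: 7% and 15% at SD 2.5 kg; 20% and 61% at SD 1.0 kg. Since 4.7 kg is already an SD of change, adjusting for baseline weight is unlikely to alter this much.

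**Step 5. The pooled comparison.** With 22 per arm, SE = 4.7 × √(2/22) = 1.42 kg, df = 42.

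| Pooled difference | Two-sided, 22 per arm | One-sided, 22 per arm | Two-sided, 28 vs 26 | One-sided, 28 vs 26 |
|---|---|---|---|---|
| 3.0 kg (12 mo) | 54% | 67% | 63% | 75% |
| 3.5 kg (24 mo) | 67% | 78% | 77% | 85% |

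**The case against.** The sentence can be read more gently. It contrasts underpowered secondary outcomes with the primary outcome, and its reference to category goals may only describe how the pooled effect was built; the Sample size section never claims power within a category. That reading is possible, so a flat statement that the article claims 80% power in healthy-weight women would go too far. It does not rescue the sentence, however. At the planned 22 per arm the pooled power falls short of 80% two-sided at both primary time points, and one-sided it is near 80% only at 24 months. It passes 80% only one-sided, for 3.5 kg, with all 54 randomised women retained.

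The category figures also rest on an SD and a control gain that the article gives only for the whole arm. The exact percentages therefore carry those assumptions, but the conclusion for healthy-weight women does not depend on them: even an SD of 1.0 kg leaves power below 80%.

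Two stronger inferences are tempting and unsupported. A reader might infer that a null healthy-weight result is all but certain whatever the truth. It is not: with 11 per arm, power is about 16% at 2 kg, 48% at 4 kg and 81% at 6 kg. A reader might also infer that the authors will present a positive pooled result as prevention of gain in healthy-weight women. The article does not say so. It defines weight control as maintenance for healthy-weight women and loss for overweight women, and it states openly that the pooled effect includes the overweight women's loss.

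For overweight women the claim roughly holds.

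**Conclusion.** The power statement in the Discussion is unsupported as written. Read by category, it fails clearly for healthy-weight women (about 6-8% two-sided at SD 4.7 kg; 7-15% at SD 2.5 kg) and is about right for overweight women (74-81%). Read as the pooled comparison only, it overstates what 22 evaluable women per arm provide: about 67% at 24 months and 54% at 12 months two-sided, or 78% and 67% one-sided. These figures assume about 11 evaluable women per arm per category, a common SD and a common control gain; the sidedness of the test is not stated.

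The practical consequence is limited but real. A non-significant healthy-weight result is likely for any difference near those the plan assumes, and is not evidence of no effect. The design and the primary analysis are not affected by this point.

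**What to change.** In the Discussion, restrict the power statement to the pooled comparison, give its recomputed value at 12 and 24 months, and state whether the test is one- or two-sided. Add that the trial is not powered within healthy-weight women, with the assumptions behind that (SD, control gain, number per arm). Report the BMI-stratified weight results planned under Data analysis as exploratory estimates with 95% confidence intervals, preferably from a single model with a group-by-category term.

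The cost is a less favourable power statement and a narrower claim. No new data and no change to the trial's conduct are needed.
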